## Methods

### Study aims

The primary aim of this study is to evaluate the effect of group antenatal care on gestational age at birth, at a cluster level. The secondary aims of this study are to determine the effects of: group antenatal care, screening obstetric ultrasound, and urine pregnancy testing in the community on antenatal care attendance and women’s and providers’ experience of antenatal and postnatal care; group antenatal care on preterm birth rates; group antenatal care on mode of birth; and group antenatal care on the outcomes of neonates at 42 days after birth, specifically among preterm neonates.

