### Outcomes and processes for comparison

This trial will evaluate both outcomes and processes. The primary study outcome is GA at birth. GA at birth will be calculated using the EDD assigned by ANC providers using the best obstetric estimate. In health centers randomized to implement basic obstetric ultrasound, this tool will be used to optimize GA assignment. In addition, postnatal measurements of every newborn will be used to estimate GA at birth and assign a corrected GA if needed.

Secondary outcomes include attendance, PTB rate, and neonatal mortality and morbidity among preterm neonates. Outcomes, including analysis metrics, method of aggregation and time points are summarized in
Table 2.

**Table 2. T2:** Outcomes.

Measurements variable	Analysis metric	Aggregation	Time Point
Primary Outcomes			
GA at birth	Average weeks completed	Health center	At delivery
Secondary Outcomes			
Preterm birth	Yes/no <37 weeks GA	Rate compared across arms	At delivery
Mortality among preterm neonates	Alive/dead	Rate compared across arms	At 28 days and 42 days, measured at six week follow up visit
Attendance at four ANC visits	Yes/no	Proportion compared across arms	At Delivery
Attendance at ANC one <14 weeks GA	Yes/no	Proportion compared across arms	At ANC 1
Attendance at PNC at six weeks	Yes/No	Proportion compared across arms	Record review at 12 weeks post EDD
Women identified as being high risk at ANC	Yes/no	Proportion compared across arms	From 1 ^st^ ANC until day of delivery
Caesarean section	Yes/no	Proportion compared across arms	At delivery
Newborn morbidities: jaundice, rapid breathing, fever, pneumonia, hypothermia, cord infection	Any reported: Yes/no	Proportion compared across arms	Reported in Rapid SMS (community reporting system) or neonatal register by 28 days of age
Other Outcomes			
Acceptability	Qualitative data on acceptability to women and providers	Qualitative reporting	At nine and 18 months
Satisfaction with care, locus of control, perceived social support, perceived stress, and depressive symptoms	Survey data	Comparison across arms	Baseline (at enrollment) and eight weeks after birth
Postnatal health behaviors, including family planning uptake, insecticide- treated mosquito net use, and breastfeeding	Survey data	Comparison across arms	Eight weeks after birth

GA, gestational age; ANC, antenatal care; PNC, postnatal care; EDD, estimated date of delivery.

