*Extended data*: File 10). Process measures of interest are the time spent on each ultrasound examination and the timing of the ultrasound (whether it was completed as part of a routine ANC visit or as a separate visit). At the community level, a UPT monthly form will be used to report on number of women tested, test results and referrals granted (
*see Extended data*: File 11)
^18^. These data will also be captured by the data collector in Research Electronic Data Capture version 2.35 (REDCap)
^23^.

Data elements are collected at enrollment (ANC 1 visit), during later ANC visits, delivery, and at PNC visits in the health center. In cases where a mother had a complication and was referred to the district hospital, usually the closest district hospital located within the catchment area, data collectors will find these data in the hospital registers. Data collectors are also responsible for monitoring the cohorts on a routine basis. This tracking process should alert staff when mothers do not attend ANC visits, give birth at a different facility, or do not attend PNC. Those who have not attended PNC by 12 weeks after the expected delivery date will be followed up by facility record review, telephone, or in immunization clinics to minimize loss to follow up.
Table 3 displays the data collection strategy for each measure that will be analyzed and reported. Data collectors will also report adverse events and protocol violations (see
*Extended data*: Files 1 and 2)
^18^.

**Table 3. T3:** Outcome main indicators and data sources.

Outcome	Outcome indicator	Analysis Group	Source
**Gestational age**	GA (Recorded GA at birth VS. LMP- calculated GA)	All live births (Apgar > 0 at 1 min)	MAT Register
**28-day infant mortality among** **preterm neonates**	Preterm neonates dead at 28 days Preterm neonates alive at 28 days Preterm neonates lost to follow-up at 28 days	All live births (Apgar > 0 at 1 min) with GA < 37 weeks	MAT & NEO Register, RapidSMS
**42-day infant mortality among** **preterm neonates**	Preterm neonates alive at 42 days Preterm neonates dead at 42 days Preterm neonates lost to follow-up at 42 days	All live births (Apgar > 0 at 1 min) with GA < 37 weeks	PNC & Immunization Register, RapidSMS
**Adherence: four ANC visits**	Women who attended four ANC	All women who attended ANC 1	ANC Register
**Adherence: six-week PNC**	Women who attended PNC 1	All women who attended ANC 1	PNC Register

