**ANC 1 within 1st trimester**	Women who attended ANC 1 <16 weeks	All women who attended ANC 1	ANC Register
**Identification of high risk**	Women with risk factors identified Number of women referred with risk factors	All women who attended ANC 1	ANC Register
**Maternal morbidity**	Cesaerean sections women referred for delivery women 'sick'	All deliveries	MAT Register, Referral Forms, RapidSMS

GA, gestational age; LMP, last menstrual period; MAT, maternity; NEO, neonatal; ANC, antenatal care; PNC, postnatal care;.

Other secondary outcomes will be measured. First, to survey a sub-set of participants across all trial arms, a convenience sample of the first five women to present for ANC per month are invited to participate in a baseline questionnaire measuring satisfaction with care, locus of control, perceived social support, perceived stress, and depressive symptoms. Similarly, among those who present at the health center with newborns approximately six weeks after birth, five women will be invited to participate in a follow-up questionnaire in which the same baseline questions are repeated and additional questions about postnatal health behaviors, including family planning uptake, insecticide-treated mosquito net use, and breastfeeding, are added
*.* This will be an unmatched cohort of survey participants and the baseline and postnatal questionnaires (see
*Extended data*: Files 3–5)
^18^. These questionnaires will be conducted in person by the data collector when the woman visits the health facility. Second, ANC and PNC providers in all arms are invited to participate in a longitudinal survey about job satisfaction, preferences, and perceived stress (baseline and follow-up questionnaires are available as
*Extended data*: Files 6–8)
^18^. These data will be collected at study training meetings or administered by data collectors at the facilities. The baseline data of providers trained to deliver group ANC/PNC will be linked to their longitudinal scores of group ANC model fidelity assessed at regular intervals by the Master Trainers (assessment tool appears as
*Extended data*: File 9)

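### Neonatal mortality is compared only among preterm live births, a group that group care is meant to change, so a shift in case mix can distort the comparison in either direction

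*Protocol article*

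**What the plan says.** **Mortality.** In the protocol article, Table 2 (Outcomes and processes for comparison) lists "Mortality among preterm neonates" as a secondary outcome, scored alive or dead at 28 and 42 days, with the rate compared across arms. Table 3 (Data collection) fixes the denominator for both time points as "All live births (Apgar > 0 at 1 min) with GA < 37 weeks". The Study aims carry the same restriction ("group antenatal care on the outcomes of neonates at 42 days after birth, specifically among preterm neonates"), and so does the outcomes text ("Secondary outcomes include attendance, PTB rate, and neonatal mortality and morbidity among preterm neonates"). Neither table has a mortality row over all live births.

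**Preterm birth.** The Study aims also name the effect of "group antenatal care on preterm birth rates" as a question, and Table 2 makes preterm birth a secondary outcome. The Introduction gives longer gestation under group care as the hypothesis.

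**Survey.** For the postnatal questionnaire, Data collection says that "among those who present at the health center with newborns approximately six weeks after birth, five women will be invited to participate". It is given in person at the facility. The same section states: "This will be an unmatched cohort of survey participants". The Abstract calls the women's survey longitudinal. Table 2 plans to compare the survey results across arms, and it lists six-week postnatal attendance as a secondary outcome.

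**The concern.** Randomization makes the arms comparable at enrollment. It does not make those who later deliver before 37 weeks comparable, because the intervention may change who belongs to that group. If group care turns some preterm births into term births, those infants leave the group-care denominator. The infants who remain may be sicker or healthier on average than the preterm infants under standard care. A ratio of deaths to preterm births then mixes any effect on survival with an effect on membership.

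This is the only mortality comparison listed. A real benefit could be published as harm, or a change in case mix as benefit. The primary outcome is not affected in this way, since Table 3 assesses gestational age over all live births.

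The postnatal survey has a milder form of the same problem. If group care brings more women back at about six weeks, the women surveyed in the two groups differ in who they are as well as in the care they received.

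**Working it through.** **The plan's own figures.** The Sample size section covers only the primary outcome. It gives no rate, effect or power for mortality or the survey, so there is no plan figure to reproduce on this point. All rates below are assumptions chosen to show direction.

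**Mortality: inputs (assumed).** Under standard care, per 100 births: 6 early preterm (10% die), 6 late preterm (2% die) and 88 term (0.5% die).

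- Preterm deaths per 100 births = early × 0.10 + late × 0.02.
- Mortality among preterm neonates = preterm deaths / (early + late).
- All deaths per 100 births = preterm deaths + term × 0.005.

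| Case | Early | Late | Preterm deaths per 100 births | Mortality among preterm | All deaths per 100 births |
|---|---|---|---|---|---|
| Standard care | 6 | 6 | 0.60 + 0.12 = 0.72 | 0.72/12 = 6.0% | 0.72 + 0.44 = 1.16 |
| A: 2 points late to term | 6 | 4 | 0.60 + 0.08 = 0.68 | 0.68/10 = 6.8% | 0.68 + 0.45 = 1.13 |
| B: as A, and 2 points early to late | 4 | 6 | 0.40 + 0.12 = 0.52 | 0.52/10 = 5.2% | 0.52 + 0.45 = 0.97 |
| C: the shift in A reversed | 6 | 8 | 0.60 + 0.16 = 0.76 | 0.76/14 = 5.4% | 0.76 + 0.43 = 1.19 |

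- Case A: deaths fall, but the planned measure rises.
- Case B: the planned measure falls in the right direction but understates the gain. Its ratio is 5.2/6.0 = 0.87, against 0.52/0.72 = 0.72 for preterm deaths per birth.
- Case C: deaths rise, but the planned measure falls.

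**Sensitivity to the assumed rates.** Take 2% early preterm (20% die), 8% late preterm (2% die) and term mortality of 0.5%. Preterm mortality under standard care is (0.40 + 0.16)/10 = 5.60%, and all-births mortality is 10.10 per 1000. Suppose group care moves a quarter of late preterm births to term. Preterm mortality becomes (0.40 + 0.12)/8 = 6.50%, and all-births mortality becomes 9.80 per 1000. Moving 10% or 50% gives 5.91% or 8.00%, with all-births mortality at 9.98 or 9.50 per 1000.

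**Survey: inputs (assumed).** Depressive symptoms affect 15% of women who would attend anyway and 30% of women who attend only because of group care. Group care truly lowers the prevalence by 2 points in every woman. With attendance a0 under standard care and e added by group care:

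observed difference = [a0 × (0.15 − 0.02) + e × (0.30 − 0.02)] / (a0 + e) − 0.15

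- Attendance 40% to 50%: (0.052 + 0.028)/0.50 − 0.15 = +1 point.
- Attendance 40% to 60%: (0.052 + 0.056)/0.60 − 0.15 = +3 points.
- Attendance 30% to 60%: (0.039 + 0.084)/0.60 − 0.15 = +5.5 points.

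Swapping the two prevalences in the first line gives (0.112 + 0.013)/0.50 − 0.30 = −5 points, which exaggerates the true 2-point benefit. Here too the direction depends on who is drawn in.

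**The case against.** - **The preterm focus is deliberate, and the preterm rate sits beside it.** Mortality related to prematurity is the initiative's stated purpose. If both are taken over live births, the preterm birth rate times preterm mortality gives preterm deaths per live birth. This stands in part: a careful reader could recover that estimate. The plan does not list it as a comparison, and deaths at term would still appear nowhere.
- **Direction.** A reader might infer that the comparison must be biased against group care if the primary hypothesis is true. The documents do not support that. The hypothesis concerns mean gestational age and does not say which preterm births are prevented. Case B gives 5.2%, below 6.0%.
- **Dating.** A reader might also infer that ultrasound dating distorts the preterm label between the main groups. Ultrasound is randomized to half of each side (Arm 2 in standard care, Arm 4 in group care), and the main analysis is Arms 1+2 against 3+4. Its presence is balanced there, so the issue is confined to subanalyses by arm.
- **The survey is openly a convenience sample under Other Outcomes.** This stands, and it is why the survey is the lesser point. The frame is also wider than formal postnatal attendance, since it takes women who present with newborns. Ruling out any comparison across arms would go further than the problem requires. The word longitudinal is not in question for the provider survey, which repeats its questionnaires.
- **All-births mortality has limits of its own.** Table 2 ties mortality to the six-week visit, the Sample size section assumes 70% follow-up, and live birth is itself settled after randomization. These limits stand and are reflected in the fix. Tracing of women not seen by 12 weeks after the expected delivery date, by records, telephone or immunization clinics, helps with vital status. It is not described as extending the survey.

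**Conclusion.** The concern holds for the mortality outcome. The only listed comparison conditions on a state that group care is meant to change, so it can show apparent harm or apparent benefit from case mix alone. In the illustration the planned measure moves from 6.0% to 6.8% while deaths fall, to 5.2% under a broader shift, and to 5.4% while deaths rise. These sizes rest wholly on assumed rates. The structural point does not: it follows from the denominator in Table 3 together with the aims. The direction in this trial cannot be known in advance.

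The survey point holds as a caveat on interpretation. Separately, the Abstract's description of the women's survey disagrees with Data collection. The primary outcome and its sample size are untouched. The mortality outcome should be changed, but the trial's main conclusion does not depend on it.

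**What to change.** **Mortality**
- Make 28-day and 42-day death among all live births of enrolled women the between-arm mortality comparison.
- Report preterm deaths per all live births beside it.
- Report completeness of 28-day and 42-day follow-up by arm.
- Keep mortality among preterm neonates as a descriptive result, read together with the preterm birth rate.

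**Survey**
- Report six-week attendance by arm beside the postnatal survey results.
- State that the results describe women who came to the health center, or weight for attendance.
- Describe the women's survey as two unmatched samples, and correct the Abstract.

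**Cost.** The mortality change means new wording and a wider denominator. All enrolled women are already to be followed to 42 days through the same registers and RapidSMS. The downside is a lower event rate: under the assumed rates, 1.16% of all live births against 6.0% of preterm births. Study status says data collection has ended and analysis is under way. These changes are still possible, but they should be dated and declared as made after data collection. Redrawing the survey sample is no longer possible and is not requested.

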### Data collection

All women enrolled in the study will be followed across pregnancy, birth, and up to 42 days after birth. We will leverage Rwanda’s existing data collection system to collect health outcomes data for the primary analysis. Specifically, we will use existing national data collection tools, including: ANC/PNC patient files; ANC, maternity, neonatal, and PNC registers; and the Rapid SMS database, a national real-time reporting and alert system which allows interactive communication between the CHW, health center, and the national centralized database, as our data sources. Given this, prior to the start of the RCT, the 36 health centers and the six district hospitals that receive referred clients from those health centers participated in data strengthening training to improve completeness, reliability and accuracy of existing data streams, especially registers and individual client files. First, the chief of nursing, the monitoring and evaluation officer and the data manager from each of the district hospitals were trained by data systems experts from the MOH, RBC and UR in a trainer-of-trainers model. Subsequently, those trained at the district level taught the same data strengthening module to data managers, CHW supervisors and ANC/PNC nurses at health centers with the support of project partners from RBC and the UR.

During the study duration, a PTBi—Rwanda data collector employed by this research team will be embedded at each study facility. These data collectors have at least an advanced diploma (A1) in general nursing or midwifery. The data collector introduces the study to each woman who presents for ANC and invites her to consent to data collection and analysis (see
*Consent to participate* section below). At sites randomized to group ANC (Arms 3 and 4), the data collector assigns each enrolled woman to an antenatal group with her peers based on GA, communicates with ANC/PNC providers and CHWs to organize each health center’s group ANC schedule. However, these data collectors do not assist during group ANC or remind pregnant women to attend visits. In Arms 2 and 4, an ultrasound report form developed for this study will document examination findings, diagnosis, and examination process measures (see
*Extended data*: File 10). Process measures of interest are the time spent on each ultrasound examination and the timing of the ultrasound (whether it was completed as part of a routine ANC visit or as a separate visit). At the community level, a UPT monthly form will be used to report on number of women tested, test results and referrals granted (
*see Extended data*: File 11)
^18^. These data will also be captured by the data collector in Research Electronic Data Capture version 2.35 (REDCap)
^23^.

Data elements are collected at enrollment (ANC 1 visit), during later ANC visits, delivery, and at PNC visits in the health center. In cases where a mother had a complication and was referred to the district hospital, usually the closest district hospital located within the catchment area, data collectors will find these data in the hospital registers. Data collectors are also responsible for monitoring the cohorts on a routine basis. This tracking process should alert staff when mothers do not attend ANC visits, give birth at a different facility, or do not attend PNC. Those who have not attended PNC by 12 weeks after the expected delivery date will be followed up by facility record review, telephone, or in immunization clinics to minimize loss to follow up.
Table 3 displays the data collection strategy for each measure that will be analyzed and reported. Data collectors will also report adverse events and protocol violations (see
*Extended data*: Files 1 and 2)
^18^.

**Table 3. T3:** Outcome main indicators and data sources.

Outcome	Outcome indicator	Analysis Group	Source
**Gestational age**	GA (Recorded GA at birth VS. LMP- calculated GA)	All live births (Apgar > 0 at 1 min)	MAT Register
**28-day infant mortality among** **preterm neonates**	Preterm neonates dead at 28 days Preterm neonates alive at 28 days Preterm neonates lost to follow-up at 28 days	All live births (Apgar > 0 at 1 min) with GA < 37 weeks	MAT & NEO Register, RapidSMS
**42-day infant mortality among** **preterm neonates**	Preterm neonates alive at 42 days Preterm neonates dead at 42 days Preterm neonates lost to follow-up at 42 days	All live births (Apgar > 0 at 1 min) with GA < 37 weeks	PNC & Immunization Register, RapidSMS
**Adherence: four ANC visits**	Women who attended four ANC	All women who attended ANC 1	ANC Register
**Adherence: six-week PNC**	Women who attended PNC 1	All women who attended ANC 1	PNC Register
**ANC 1 within 1st trimester**	Women who attended ANC 1 <16 weeks	All women who attended ANC 1	ANC Register
**Identification of high risk**	Women with risk factors identified Number of women referred with risk factors	All women who attended ANC 1	ANC Register
**Maternal morbidity**	Cesaerean sections women referred for delivery women 'sick'	All deliveries	MAT Register, Referral Forms, RapidSMS

GA, gestational age; LMP, last menstrual period; MAT, maternity; NEO, neonatal; ANC, antenatal care; PNC, postnatal care;.

Other secondary outcomes will be measured. First, to survey a sub-set of participants across all trial arms, a convenience sample of the first five women to present for ANC per month are invited to participate in a baseline questionnaire measuring satisfaction with care, locus of control, perceived social support, perceived stress, and depressive symptoms. Similarly, among those who present at the health center with newborns approximately six weeks after birth, five women will be invited to participate in a follow-up questionnaire in which the same baseline questions are repeated and additional questions about postnatal health behaviors, including family planning uptake, insecticide-treated mosquito net use, and breastfeeding, are added
*.* This will be an unmatched cohort of survey participants and the baseline and postnatal questionnaires (see
*Extended data*: Files 3–5)
^18^. These questionnaires will be conducted in person by the data collector when the woman visits the health facility. Second, ANC and PNC providers in all arms are invited to participate in a longitudinal survey about job satisfaction, preferences, and perceived stress (baseline and follow-up questionnaires are available as
*Extended data*: Files 6–8)
^18^. These data will be collected at study training meetings or administered by data collectors at the facilities. The baseline data of providers trained to deliver group ANC/PNC will be linked to their longitudinal scores of group ANC model fidelity assessed at regular intervals by the Master Trainers (assessment tool appears as
*Extended data*: File 9)
^18^. Third, we will also conduct qualitative research among women and providers at nine and 18 months after implementation to inform program improvement. Four to six focus groups for women and four to six focus groups for providers will be convened to better understand their experiences of group ANC and PNC. More specifically, focus groups with providers will allow nurses and midwives to freely verbalized their ideas and concerns about group ANC and PNC, emphasizing on group care effect on their work, possible keys to success, effect on mothers and program changes or improvements. Focus groups with women will seek to capture reasons women will choose to attend or not group ANC and PNC, as well as soliciting suggestions to strengthen the program.

Data collectors abstract data from health center registers and patient files (and, where applicable, ultrasound reports and urine pregnancy test results) into REDCap loaded on password-protected tablet devices. Data will be synced weekly into the database via Wi-Fi network. The same devices will be used to record information from the participant and provider surveys and synced to the web-based application. Study personal identifiers will be separated from the rest of the data to ensure data protection and confidentiality. Access to the database will only be given to members of the study team. All personal information about enrolled participants will not be shared with any third party during and after the trial.

Focus group discussions will be audio recorded. To ensure confidentiality, each participant will be assigned a number; facilitators will refer to theses numbers when calling on participants during discussion. Audio files will be stored on password protected computer, only authorized staff will have access to the files. Audio recordings will be destroyed after transcription and analysis are complete.

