### Study interventions

The desire to implement group ANC in this setting required the reconsideration or customization of an intervention that has been well-defined in the context of trials in high-income economies. In most trials of group ANC, the intervention is the trademarked product CenteringPregnancy®
^21^, but for three reasons we did not assume that the existing intervention could be applied ‘off-the-shelf” in Rwanda. First, the number of visits in the CenteringPregnancy® package is greater than the number of visits recommended in the Rwanda ANC package; second, the last Demographic and Health Survey estimated that one-third of Rwandan women could not read or write well;
^17^ and finally, the unique language (Kinyarwanda) and cultural context called for customized discussion activities.

The Rwanda group ANC/PNC model was customized by the Technical Working Group, which is composed of representatives from maternal-child health stakeholder organizations in Rwanda; that model development process is described separately
^22^. Key characteristics of the Rwanda group ANC/PNC model appear in
Box 1. Despite the 2016 WHO ANC recommendations
^16^, the total number of ANC visits recommended in Rwanda is four. Of the four total PNC visits recommended in Rwanda, only PNC 4 (at approximately six weeks after birth) is a group visit. The other PNC visits do not lend themselves to a group arrangement and remain unchanged. PNC 1 is completed before facility discharge within 24 hours after delivery, and PNC visits 2 and 3 are conducted at home by community health workers.

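### Table 3 measures six-week PNC attendance by PNC 1, which the protocol defines as the pre-discharge check, and Tables 2 and 3 give different cut-offs for early ANC

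*Protocol article*

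**What the plan says.** **Six-week PNC.** Table 2 (Outcomes and processes for comparison) lists the secondary outcome "Attendance at PNC at six weeks", yes or no, from a record review 12 weeks after the EDD. Table 3 (Data collection), which is introduced as covering every measure to be analysed, has a row labelled "Adherence: six-week PNC". Its indicator is "Women who attended PNC 1", its denominator is all women with an ANC 1 visit, and its source is the PNC register. The numbering of visits is fixed under Study interventions: "PNC 1 is completed before facility discharge within 24 hours after delivery", and "only PNC 4 (at approximately six weeks after birth) is a group visit".

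**Early ANC.** Table 2 has "Attendance at ANC one <14 weeks GA". Table 3 has a row labelled as first-trimester ANC 1, with the indicator "Women who attended ANC 1 <16 weeks".

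**Newborn morbidity.** The text above Table 2 names "neonatal mortality and morbidity among preterm neonates" among the secondary outcomes. The newborn-morbidity row of Table 2 carries no preterm restriction, and Table 3 has no row for it.

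**The concern.** Table 3 is where an analyst or data manager would look to derive each variable. In the PNC row, the label and the indicator point to different visits about six weeks apart. Only the later one is delivered as a group visit. The Discussion presents the effect on six-week attendance as one of the trial's main contributions, and the Introduction says that no figure for PNC at about 42 days has yet been reported. A variable built on PNC 1 would not answer that question.

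For early ANC, the visit is the same in both tables but the threshold is not. Earlier attendance is the stated goal of the community pregnancy testing in Arms 2 and 4, and the Discussion promises a result on it. According to Study status, data collection has ended and analysis is under way. Two published thresholds therefore leave room to choose between them after the data have been seen.

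**Working it through.** **1. Which visit does the PNC row measure?**

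| Place | What it refers to |
|---|---|
| Table 2, outcome | PNC at six weeks |
| Table 3, row label | PNC at six weeks |
| Table 3, indicator | PNC 1 |
| Study interventions, definition of PNC 1 | Before discharge, within 24 hours of delivery |
| Study interventions, definition of PNC 4 | About six weeks after birth, the only group PNC visit |
| Discussion, stated question | Attendance at six-week PNC |

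Only the Table 3 indicator departs from the six-week visit. If it were applied literally, a woman seen before discharge who never returned would count as adherent. A woman who gave birth without that check but came at six weeks would count as non-adherent. The indicator and the outcome agree only for women who attended both visits or neither.

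**2. How large is the PNC error?** It cannot be computed. The article gives no six-week attendance rate and no joint distribution of the two visits.

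**3. Which early-ANC cut-off applies?** Table 2 says 14 weeks and Table 3 says 16. The first-trimester label in Table 3 sits better with 14. On the other side, 16 weeks is the threshold in the pair-matching criteria (Study design), the ideal timing of ANC 1 in Table 1, and the background figure in the Introduction. The document does not settle it.

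**4. How far apart are the two early-ANC definitions?** The only input is the Introduction's 56% of women entering ANC before 16 weeks. Women attending before 14 weeks are a subset of these, so 0% ≤ P(<14) ≤ 56%. The document supports no narrower bound.

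**5. Does either conflict reach the sample size?** No. The stated figure concerns GA at birth and reproduces from its own inputs (SD 4.3 weeks, ICC 0.01, difference 0.5 weeks, 36 facilities, 214 observations each):

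- Design effect = 1 + (214 − 1) × 0.01 = 3.13.
- Effective n per side = 18 × 214 / 3.13 = 3852 / 3.13 = 1230.7.
- Power at two-sided 5% = 80.0% (noncentral t, 34 df).
- Recruits per facility = 214 / 0.70 = 305.7, so 306. Over 36 facilities, 306 × 36 = 11,016.

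Neither disputed definition enters these steps.

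**The case against.** The strongest reply is that PNC 1 is a slip in one cell. The label of the same row, Table 2, the follow-up of women without PNC by 12 weeks after the expected date, and the Discussion all point to the six-week visit. The row's source, the PNC register, is also the one Table 3 uses for 42-day mortality, whereas 28-day mortality draws on the maternity and neonatal registers. This is persuasive about intent, and it means that the outcome is miscomputed only if the cell is followed. It does not make the cell right.

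Several stronger readings are tempting, but the document does not support them:

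- *Both outcomes would be computed on the wrong event.* For early ANC the event is the same and only the cut-off differs.
- *These are key outcomes.* The article calls them secondary and ranks none as key.
- *A PNC 1 comparison would show almost no difference between arms, because 91% of births are in facilities and group care leaves PNC 1 alone.* The Introduction also reports that only about 19% of newborns are assessed in the first two days, so recorded early PNC does not simply follow facility birth. An unchanged format also does not prove unchanged attendance, since the group curriculum includes a birth plan.
- *The level of the early-ANC outcome shifts by 16 to 26 points.* That range needs an assumed normal distribution with an SD of 3 to 5 weeks, which gives 40% to 30% before 14 weeks. The article supports neither the shape nor the SD. A shift in level is also not a bias between arms.
- *14 weeks is the correct cut-off.* Table 2 and the first-trimester label favour it, but the uses of 16 weeks elsewhere leave it open.

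On newborn morbidity, the text introduces a list that need not be exhaustive, and Study aims speaks of neonates with a particular focus on preterm ones. That conflict is minor.

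**Conclusion.** The point holds as two conflicts in the definitions of secondary outcomes. The PNC conflict is the more serious. By the article's own numbering, the Table 3 indicator is a different visit from the outcome it is meant to measure, and the outcome is a stated aim of the trial. The early-ANC conflict is an unresolved choice between two cut-offs, which matters because it could be settled after the data are seen. Neither touches the primary outcome or the sample size. The effect on the secondary results cannot be quantified from the document. The conclusion rests on reading Table 3 as written; nothing in the article shows that the variables have actually been coded that way.

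**What to change.** 1. In Table 3, replace PNC 1 in the six-week row with the six-week PNC visit (PNC 4), and check that the derived variable uses that visit.
2. Reconcile Tables 2 and 3 to one early-ANC cut-off, fixed and recorded before arms are compared, and report the other descriptively. If arms have already been compared, say so and report both.
3. As a minor item, state one population for newborn morbidity in the text and in Table 2: all newborns, preterm newborns, or all with preterm as a named subset.

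The cost is a correction to the tables and a check of the coding. No new data are needed.
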